## Abstract

**Background:**

Open transthoracic oesophagectomy is the standard treatment for infracarinal resectable oesophageal carcinomas, although it is associated with high mortality and morbidity rates of 2 to 10% and 30 to 50%, respectively, for both the abdominal and thoracic approaches. The worldwide popularity of laparoscopic techniques is based on promising results, including lower postoperative morbidity rates, which are related to the reduced postoperative trauma. We hypothesise that the laparoscopic abdominal approach (laparoscopic gastric mobilisation) in oesophageal cancer surgery will decrease the major postoperative complication rate due to the reduced surgical trauma.

**Methods/Design:**

The MIRO trial is an open, controlled, prospective, randomised multicentre phase III trial. Patients in study arm A will receive laparoscopic-assisted oesophagectomy, i.e., a transthoracic oesophagectomy with two-field lymphadenectomy and laparoscopic gastric mobilisation. Patients in study arm B will receive the same procedure, but with the conventional open abdominal approach. The primary objective of the study is to evaluate the major postoperative 30-day morbidity. Secondary objectives are to assess the overall 30-day morbidity, 30-day mortality, 30-day pulmonary morbidity, disease-free survival, overall survival as well as quality of life and to perform medico-economic analysis. A total of 200 patients will be enrolled, and two safety analyses will be performed using 25 and 50 patients included in arm A.

**Discussion:**

Postoperative morbidity remains high after oesophageal cancer surgery, especially due to major pulmonary complications, which are responsible for 50% of the postoperative deaths. This study represents the first randomised controlled phase III trial to evaluate the benefits of the minimally invasive approach with respect to the postoperative course and oncological outcomes in oesophageal cancer surgery.

**Trial Registration:**

NCT00937456 (ClinicalTrials.gov)

## Background

Surgery is viewed as the best treatment for resectable thoracic oesophageal cancer (OC) with a 5-year survival rate of around 40% in patients resected with a curative intent [1,2]. Oesophagectomy using the abdominal and right-thoracic approach (Ivor-Lewis procedure) is considered to be the standard technique for middle- and lower-third thoracic OC, which represent the most frequent locations for OC, allowing for optimal loco-regional control and long-term survival. However, despite advances in surgical and perioperative management, postoperative morbidity, especially pulmonary complications, remains high and is reportedly between 30 and 50%, with a significant postoperative mortality between 2 and 10% [1].

Minimally invasive oesophagectomy (MIO) has been attempted during the last decade with the aim of improving the postoperative outcomes without compromising oncological outcomes. MIO corresponds to a collection of techniques that combine thoracoscopic and/or laparoscopic approaches, including hybrid MIO (HMIO) (laparoscopy/thoracotomy or laparotomy/thoracoscopy) and total MIO (laparoscopy/thoracoscopy). These methods have had controversial impacts on the postoperative course, and few data are available regarding the oncological outcomes [3-5].

To date, no randomised trials have been published, and the few retrospective comparative cohort studies that are available are limited by small sample sizes [6-8], major selection biases that make it impossible to compare study groups [9] and/or an absence of a rigorous definition of complications.

The thoracoscopic approach has received greater attention than laparoscopy. In the systematic reviews that have been published, thoracoscopic resections were found to have marginal benefits over open resections, such as reduced blood loss and transfusion rates and a shorter hospital stay. However similar morbidity profiles were observed, especially regarding pulmonary complications, which are the main postoperative complications after oesophagectomy [3,4]. A multicentre randomised trial (the TIME Trial) has recently been designed to study the impact of MIO (thoracoscopy and laparoscopy versus thoracotomy and laparotomy) in OC surgery, but multiple surgical procedures are proposed and there is an absence of perioperative care standardisation [10].

Laparoscopy has not been widely studied, although this technique may offer several advantages, including a lower rate of pulmonary complications (due to the less invasive nature of the procedure and reduced deterioration of the ventilatory mechanism than is observed after the open procedure [11]), ease of performance and reproducibility in specialised and non-specialised centres, the absence of laparoscopic tumoural dissection and the consequent applicability to a large number of patients regardless of the tumoural stage or neoadjuvant treatment and a lower risk of impairment of the oncological outcomes.

Several retrospective studies have suggested that HMIO with laparoscopic gastric mobilisation is feasible in OC, but these studies have major flaws, such as non-comparable groups, a small number of enrolled patients, the lack of a control group and neither pulmonary complications nor long-term outcomes considered as primary endpoints [12-16].

Because the vast majority of published studies have placed a higher priority on demonstrating feasibility than evaluating the impact on patients, and because of inconclusive results regarding the benefits of MIO with respect to outcomes, we aim to test the hypothesis that HMIO based on laparoscopic gastric mobilisation and open thoracotomy decreases major postoperative morbidity without compromising oncological outcomes through a large prospective randomised controlled trial.

## Methods/Design

### 1- Protocol overview (Figure 1)

**Figure 1 F1:**
[figure not shown]
**Study flow chart**.

The MIRO trial is a prospective multicentre controlled randomised phase III trial comparing HMIO (with laparoscopic gastric mobilisation and open thoracotomy) and open oesophagectomy (with open gastric mobilisation and thoracotomy) in patients with thoracic OC who undergo oesophagectomy through the abdominal and right-thoracic approach (Ivor-Lewis procedure). In both arms of the study, patients will undergo an open-right thoracic approach. After a complete preoperative work-up and according to French national guidelines, patients who are found to be eligible for an Ivor-Lewis procedure (staged I, II or III, i.e., T1,T2,T3, N0 or N1, M0) with or without neoadjuvant treatment will be considered eligible for inclusion in this study. The surgical procedure will be scheduled 4 to 6 weeks after the completion of the neoadjuvant treatment, or within 4 weeks following the preoperative work-up in cases of primary surgery. Randomisation will be performed during the surgical procedure after a laparoscopic exploration of the abdominal cavity to confirm the absence of any contra-indication for resection. Patients in arm A will undergo HMIO, and patients in arm B will undergo traditional open oesophagectomy.

The primary endpoint is the major morbidity rate occurring within 30 postoperative days, the two groups will be compared regarding the postoperative course and oncological outcomes.

Our primary hypothesis is that HMIO will reduce major postoperative morbidity compared to the open approach.

This study is planned for a 5-year duration with a 2-year inclusion period and a 3-year follow-up period for the last included patient. The results for the primary endpoint will be available 1 month after the end of the inclusion period.

### 2- Inclusion criteria

This study will include patients with squamous cell carcinoma (SCC) or adenocarcinoma (ADC) of the middle or lower third of the oesophagus and who are eligible for surgery.

The inclusion criteria are as follows: (i) patients with SCC or ADC of the thoracic oesophagus staged I, II or III (T1, T2, T3, N0 or N1, M0) before any treatment; (ii) patients with OC in the middle or lower third or junctional Siewert's type I tumour; (iii) patients who are undergoing or not undergoing neoadjuvant radiotherapy and/or chemotherapy; (iv) patients with tumours deemed to be resectable with a curative intent at the preoperative evaluation; (v) patients who are over 18 and under 75 years of age; (vi) patients with WHO status performance of 0, 1 or 2; (vii) patients who provide a signed written consent form; (viii) patients who can undergo one of the surgical modalities to be investigated; and (ix) patients who will be available for follow-up.

### 3- Exclusion criteria

All patients who do not meet all the inclusion criteria will be excluded. The other exclusion criteria are the common contraindications for surgery related to patient status, disease extension or operative technique.

The patient-associated exclusion criteria are patients with the following features: (i) PaO2 < 60 mmHg, (ii) Pa CO2 > 45 mmHg, (iii) FEV1 < 1000 ml/sec, (iv) cirrhosis, (v) myocardial infarction or evolutive coronary artery disease, (vi) Leriche-Fontaine at stage II or more peripheral arterial occlusive disease, (vii) weight loss exceeding 15%, (viii) the presence of another malignant tumour within the last 5 years or a synchronous malignant tumour, and (ix) any other simultaneous experimental treatment.

The disease-associated exclusion criteria are (i) another histological subtype of OC besides SCC or ADC, (ii) tumours located at the pharyngoesophageal junction, the cervical oesophagus, the upper third of the oesophagus, or the oesophagogastric junction (types 2 or 3 of the Siewert's classification), (iii) distant metastases, including peritoneal carcinomatosis or metastasis to the supra-clavicular and celiac lymph nodes, (iv) recurrent nerve palsy, (v) tumoural involvement of adjacent mediastinal structures.

The surgical technique-associated exclusion criteria are (i) contra-indication for laparoscopy and (ii) a history of supra-umbilical laparotomy.

### 4- Endpoints

The primary endpoint is the major pre- and postoperative morbidity rate (occurring within 30 postoperative days). Major pre- and postoperative morbidity is defined as grade 2 (potentially life-threatening but not causing residual disability and requiring medical or invasive procedures), grade 3 (causing residual disability, including organ resection or persistence of life-threatening conditions) and grade 4 (death as a result of complications) surgical and medical complications, according to the Dindo-Clavien classification [17]. The most severe complications will be considered for the primary endpoint. However, the total number of complications per patient will also be monitored.

Secondary endpoints are postoperative mortality, postoperative overall 30-day morbidity (major and minor), the major pulmonary complication rate, disease-free survival (DFS: defined as the time interval between randomisation and the first recurrence (local, regional, distant), second cancer or death), overall survival (OS: defined as the time interval between randomisation and all deaths), quality of life (evaluated using the EORTC quality of life (QoL) questionnaires QLQ-C30 and QLQ-OES18, and EuroQol 5D) and the global economic impact of each surgical procedure.

A standardised definition of the main complications, especially pulmonary complications, are as follows:

- anastomotic leakage, defined as a symptomatic (mediastinal abscess, mediastinitis or digestive flow in chest drainage) or asymptomatic (diagnosed by water-soluble contrast swallow or digestive endoscopy) disruption of the intrathoracic anastomosis;

- gastric pull-up necrosis, defined as ischemia requiring a surgical procedure and a partial or complete removal of the gastric conduit;

- delayed gastric emptying, defined as iterative vomiting after nasogastric tube removal (from day 5), despite prokinetic treatment, requiring nasogastric tube re-placement;

- recurrent laryngeal nerve palsy;

- major postoperative pulmonary complications are defined as follows:

◦ major bronchic sputum, defined as bronchic sputum with atelectasis requiring bronchoscopy and lack of fever or hyperleukocytosis;

◦ pneumonia, defined as alveolo-interstitial radiologic infiltration with the presence of at least two of the following criteria: purulent sputum, temperature > 38.5°C or < 35°C or leukocytes > 10000/mm^3 ^or < 1500/mm^3^;

◦ respiratory insufficiency, defined as the inability of a patient to maintain a PaO2 > 60 mmHg or a PaCO2 < 55 mmHg, requiring an oro-tracheal intubation and assisted ventilation;

◦ the presence of Acute Respiratory Distress Syndrome (ARDS), defined as severe hypoxia (PaO2/FiO2 < 200), diffuse bilateral pulmonary infiltration and pulmonary wedge pressure less than 18 mmHg. Acute lung injury, defined as PaO2/FiO2 between 200 and 300, is considered ARDS.

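### The major pulmonary complication definitions do not join: atelectasis needing bronchoscopy, with fever and/or hyperleukocytosis but short of pneumonia, can fall in no category

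*Protocol article*

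**What the plan says.** Section 4 (Endpoints) gives standardised definitions of the main complications, including four categories of major pulmonary complication:

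- bronchial secretions: "major bronchic sputum, defined as bronchic sputum with atelectasis requiring bronchoscopy and lack of fever or hyperleukocytosis";
- pneumonia: "alveolo-interstitial radiologic infiltration with the presence of at least two of the following criteria", the criteria being "purulent sputum, temperature > 38.5°C or < 35°C or leukocytes > 10000/mm"³ or, at the low end, below 1500/mm³;
- respiratory insufficiency, defined by failure to hold blood gases and "requiring an oro-tracheal intubation and assisted ventilation";
- ARDS, "defined as severe hypoxia (PaO2/FiO2 < 200), diffuse bilateral pulmonary infiltration" and a limit on wedge pressure, with acute lung injury (ratio 200 to 300) counted as ARDS.

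The secondary endpoints in the same section include "postoperative overall 30-day morbidity (major and minor), the major pulmonary complication rate". The abstract uses a broader label, "30-day pulmonary morbidity". The primary endpoint does not use the four categories: it takes surgical and medical complications of severity grade 2 to 4 within 30 days.

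**The concern.** Categories that together define one event should join, so that a patient with more signs of disease is not less likely to be counted. Here the first category is closed off by fever and hyperleukocytosis, while pneumonia opens only with an infiltrate and two signs. Patients between the two can be lost, and an added inflammatory sign can remove an event that would otherwise be recorded.

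Two features of the wording add to this. The first definition gives no threshold for fever or hyperleukocytosis, whereas pneumonia has numerical limits. The word *or* in its last clause can also be read in two ways: neither sign is present, or the two are not both present. Centres may therefore classify the same patient differently, in a trial that is open.

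The endpoint matters to the trial's argument. The Discussion gives a lower expected rate of pulmonary complications as the first reason for the hypothesis. The Background faults earlier studies for loosely defined complications, and the Discussion says that this trial has standardised its definitions across centres.

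**Working it through.** The plan gives no figure for this endpoint. Its sample size of 98 per group concerns the primary endpoint and plays no part here. The check is a full enumeration of the definitions.

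**Population considered.** Patients with bronchial secretions and atelectasis needing bronchoscopy, without respiratory insufficiency, ARDS or acute lung injury. Patients who reach those last states are counted anyway.

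**Inputs, all from section 4.** Infiltrate (yes/no), purulent sputum (yes/no), fever F (yes/no), hyperleukocytosis L (yes/no): 2 × 2 × 2 × 2 = 16 combinations. Abnormal temperature and leukocytes are taken as raised, and the two pneumonia signs are treated as the same F and L as in the first definition. That is an assumption, because the first definition sets no limits.

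**Rules.**

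- Pneumonia (P): infiltrate present, and purulent + F + L ≥ 2.
- Bronchial secretions (S), reading 1: neither F nor L.
- Bronchial secretions (S), reading 2: not both F and L.

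**Result.** Each cell shows reading 1 / reading 2.

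| Infiltrate | Purulent | Neither F nor L (1 combination) | Exactly one of F, L (2 combinations) | Both (1 combination) |
|---|---|---|---|---|
| no | no | S / S | none / S | none / none |
| no | yes | S / S | none / S | none / none |
| yes | no | S / S | none / S | P / P |
| yes | yes | S / S | P / P and S | P / P |

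**Counts.**

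- Reading 1: S covers 4, P covers 4, with no overlap. Uncovered: 16 − 4 − 4 = 8. Of these, 6 have no infiltrate and 2 have one.
- Reading 2: S covers 12, P covers 4, and 2 are in both. Covered: 12 + 4 − 2 = 14. Uncovered: 16 − 14 = 2. Both have fever and hyperleukocytosis without an infiltrate.

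**The reversal.**

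- Reading 1, infiltrate present, sputum not purulent: with neither F nor L the patient is counted (S). With one of them the patient is not counted. With both the patient is counted again (P).
- Reading 2, no infiltrate: with F or L alone the patient is counted (S). Adding the other removes the patient.

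**After the change proposed below.** S becomes every combination that is not P: 16 − 4 = 12. Then 12 + 4 = 16, with no combination uncovered and none in both.

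**The case against.** The strongest reply is that the gap depends on the reading and touches little. If the clause means that the two signs are not both present, a patient with only one of them is still counted and the gap shrinks from 8 combinations to 2. This stands as a limit on size, but it does not remove the gap. A standardised definition that yields 8 or 2 depending on the reader also needs repair.

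Several stronger inferences are tempting, and the document does not support them.

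- *A particular leukocyte count, such as 12 000/mm³, excludes a patient.* The first definition has no threshold. Applying pneumonia's 10 000/mm³ limit to it is an assumption.
- *Any single inflammatory sign excludes a patient.* Purulent sputum alone does not. Only fever or hyperleukocytosis can. Even under reading 1, only 4 of the 8 uncovered combinations have exactly one of the three signs.
- *The sickest patients drop out.* Intubated patients and those with ARDS or acute lung injury are still counted. Those lost are sicker only relative to the otherwise identical patient without fever or hyperleukocytosis.
- *The primary endpoint is compromised.* It is graded by severity and includes complications that needed medical or invasive procedures, so these patients can still count there. Overall 30-day morbidity can capture them too.
- *Half of such patients are lost.* The combinations are not equally frequent, and no frequencies are given. A patient followed for 30 days may also meet the pneumonia criteria at another time.
- *The arms are biased through inflammatory markers.* The definitions are the same in both arms, and the document gives no data on such markers by approach.

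**Conclusion.** The concern holds, limited to one secondary endpoint. As written, the categories leave out some patients who need bronchoscopy for atelectasis and have fever and/or hyperleukocytosis short of pneumonia, while otherwise identical patients without those signs are counted. The gap is 8 of 16 logical combinations if the clause means neither sign, and 2 of 16 if it means not both, so it exists on either reading.

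This rests on treating the pneumonia criteria as three separate signs, abnormal values as raised, and fever and hyperleukocytosis as the same signs in both definitions. It is a fault in a rule that the article states in operational form, not a detail left to another document. The number of patients affected, and the size and direction of any effect on the comparison of arms, cannot be derived from the document.

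**What to change.** In the first category, replace the closing clause on fever and hyperleukocytosis with *and not meeting the pneumonia criteria*. This closes the gap under both readings and removes the undefined thresholds and the ambiguous *or*.

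State also that each patient counts once in the rate of major pulmonary complications, whichever categories are met. The revised category would exclude only pneumonia, so overlap with respiratory insufficiency or ARDS remains possible.

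The cost is one line in the endpoint definitions and the matching line in the case report form guide. No new data are needed. Because the change only adds combinations, the observed rate cannot fall. A slightly higher rate in both arms is expected, though the document gives no figure from which to calculate the rise.

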### 5- Randomisation

Patients will be randomised during the operative procedure after performing a laparoscopic exploration of the abdominal cavity to confirm the absence of contra-indications for surgery (hepatic cirrhosis, hepatic or peritoneal metastasis, or non-resectable tumoural extension).

For patients in arm A, HMIO will be performed with a laparoscopic gastric mobilisation followed by an open thoracotomy. For patients in arm B, traditional open oesophgectomy will be performed with open gastric mobilisation through a midline laparotomy followed by an open thoracotomy.

The randomisation will be performed using the stratified block randomisation method (blocks of 4) for each centre. A randomised list will be generated for each centre and envelopes will be prepared and blinded for allocation during surgery according to serial inclusion.

### 6- Preoperative work-up

Patients with resectable OC will be considered to be operable after a complete pre-therapeutic work-up, which includes a physical examination, standard laboratory tests, an ear, nose and throat (ENT) examination, a panendoscopy under general anaesthesia and a bronchial fibroscopy with biopsies for SCC, an oesophagogastroduodenoscopy with biopsies and oesogastroduodenal barium study, an ultrasound exploration of the cervical and abdominal areas, a computed tomography (CT) scan of the thorax, mediastinum and abdomen; an oesophageal endoscopic ultrasound (EUS) examination, and a positron emission tomography if required. Clinical tumoural staging (cTNM) will be based on the data obtained from CT scan, EUS and positron emission tomography results.

### 7- Treatment methods

Perioperative procedures will be standardised independently of the approach.

#### - Global preoperative care

For all patients in the study, we will (i) treat dental, head and neck or bronchial infection, (ii) administer Immunonutrition (Oral Impact^®^, Nestlé Nutrition) 5 to 7 days prior to surgery, (iii) request cessation of smoking and drinking for at least 1 month before surgery and (iv) perform a percutaneous gastrostomy for artificial nutrition for malnourished patients (more than 10% of physical weight loss over a 6-month period).

#### - Anaesthesiology

Hydroxyzin (1 mg per kg) will be administered as a premedication 2 hours before surgery. Patients will receive standard monitoring. Two peripheral and one central venous catheters will be placed. Arterial catheter placement for continuous monitoring of the arterial blood pressure is optional. A thoracic epidural analgesia will be placed before induction of general anaesthesia. A test injection of 2 ml of xylocain with 2% adrenalin will be performed after the placement of the epidural catheter. Induction of general anaesthesia will be performed with intravenous injection of propofol (2 to 3 mg/kg), sufentanil (0.2 to 0.3 μg/kg) and cis-astracurium (0.1 to 0.15 mg/kg). Patients will be intubated with a left double-lumen endotracheal tube for single-lung ventilation during the thoracic approach. Antibioprophylaxis will be administered during induction with a second generation cephalosporin. General anaesthesia will be maintained with halogen gas (sevofluran or desfluran). Preoperative analgesia will be based on administration of 5 to 10 ml of 0.75% of ropivacain in the peridural catheter. During the thoracic wound closure, a continuous perfusion of 0.2% ropivacain (6 to 8 ml/h) will be started. Myorelaxation will be obtained with intravenous boluses of cis-atracurium (0.03 mg/kg) to maintain a maximum of two responses to the train-of-four stimulation. Protective ventilation will be performed with a small tidal volume (8 ml/kg), a respiration frequency of 10 to 15 cycles/min, an inspiration/expiration ratio of1/2, a FiO2 from 50 to 100%, and a positive end-expiratory pressure around 5 cmH20. Ventilation will be adjusted to maintain PaCO2 between 35 and 40 mmHg, venous oxygen saturation over 92% and a level of maximal pressure less than 50 cmH2O. Intravenous administration of fluids and electrolytes will be performed according to a relatively restricted regimen with 4 to 5 ml/kg/h of Ringer solution. Blood loss will be compensated by colloid administration and, if necessary, red blood cell transfusion to maintain haemoglobin levels from 7 to 10 g/dl. Early extubation will be performed at the end of the surgical procedure in normothermic patients.

